### Suspension and exit criteria

2.8

Patients will have the right to exit from this study. They will be treated with conventional treatment still once they withdraw the trial. Any reason of subjects exiting will be recorded in their case report file. The criteria of suspension and exit in the study will be as follows: there are serious adverse events or complications during the clinical trial; the without good compliance, subjects use drugs prohibited in this study; researchers argue that the trial may be harmful to the patient's body, mind, economy; the subjects, unwilling to the study, request to suspend the clinical trial.

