### Outcomes measure

3.2

The following outcomes for the subjects will be assessed by independent researchers who do not know the allocation.

Primary outcomes: The primary outcomes are the change from the baseline in FVC at week 4, 12, 24 and times of acute exacerbations at week 4, 12, 24.

Secondary outcomes:

1.The change from baseline in the St. George's respiratory questionnaire total score at week 4, 12, and 24.2.The change from baseline in forced expiratory volume in 1 second percentage/FVC at week 4, 12, and 24.3.The change from baseline in diffusing capacity of Carbon monoxide at week 4, 12, and 24.4.The change from baseline in brain natriuretic peptide at week 4, 12, and 24.5.The change from baseline in curative effect of TCM syndrome at week 4, 12, and 24.

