### Adverse events

3.5

Adverse events of patients will be recorded in case report files. If a serious adverse event occurs, the intervention will be suspended immediately after evaluation of researchers. Then, we will keep records of the details about the time of occurrence, the severity of condition and the relation of drugs. All measures will be recorded in accordance with standard operational procedures of the China Food and Drug Administration. Besides, serious adverse events will be made known to the Steering Committee and Ethics Committee within a day.

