### Statistical analysis

3.6

The data will be analyzed by the SPSS V.23.0 (Chicago, IL) software package after the collection of data from the entire sample. All the *P*-values will be for 2-sided distributions, with a significant level of .05 for α. A descriptive analysis of the baseline date of the sample will be performed. All the quantitative variables will be analyzed by the Kolmogorov-Smirnov test with Lilliefors corrections, to ascertain whether the variables follow a normal distribution or not. The initial homogeneity between the groups will be also analyzed (ANOVA or Kruskal–Wallis depending of the normality of data distribution).

The measurement data will be examined using group *t*-tests or non-parametric tests, the count data will be tested using a Chi-square test or Fisher exact probability method, and the grade data will be tested using nonparametric tests.

All data analyses will be conducted with the intention to treat principles. If there are losses of follow-up, the outcome variables that have not been recorded will be completed with the last data recorded for each subject of these data.

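### The exit criteria do not separate stopping study granules from leaving the study, so both primary outcomes may go unobserved after a serious event, poor compliance or prohibited drug use

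*Protocol article*

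**What the plan says.** Section 2.8 (Suspension and exit criteria) introduces a single list: "The criteria of suspension and exit in the study will be as follows". Its first item is that "there are serious adverse events or complications during the clinical trial". The next reads "the without good compliance, subjects use drugs prohibited in this study". The remaining items are the researchers' judgement of harm and the patient's own request. On what follows, the section says "They will be treated with conventional treatment still once they withdraw the trial" and asks that the reason be recorded. It mentions no outcome assessment after that.

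Section 3.5 (Adverse events) deals with one of the same triggers differently: "If a serious adverse event occurs, the intervention will be suspended immediately after evaluation of researchers". It says nothing about leaving the study.

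Section 3.2 (Outcomes measure) has two primary outcomes: change in FVC at weeks 4, 12 and 24, and "times of acute exacerbations at week 4, 12, 24".

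Section 3.6 (Statistical analysis) states: "All data analyses will be conducted with the intention to treat principles". Unrecorded outcomes after loss to follow-up are replaced by the patient's last recorded value.

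**The concern.** Stopping a treatment and ending observation are different events, and section 2.8 covers both with one list. If staff read the list as grounds for leaving the study, outcome collection ends for reasons linked to prognosis (serious events, complications) and to treatment (tolerability, compliance, use of other drugs). These can differ between arms.

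Both primary outcomes are exposed. A severe acute exacerbation could be judged a serious adverse event or a complication, and nothing in section 2.8 exempts it. The event itself would still be counted, but later exacerbations and later FVC would not. Carrying the last value forward then holds FVC at a level that probably predates the decline, and freezes a cumulative exacerbation count at its value on exit. The value of intention to treat lies in observed outcomes for everyone randomised, and those are the data that would be missing. No analysis plan can recover measurements that were never taken.

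**Working it through.** **Sections side by side.**

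| Situation | Section 2.8 | Section 3.5 | Section 3.6 |
|---|---|---|---|
| Serious adverse event | suspension or exit, not specified which | intervention suspended | analysed as randomised; gaps carried forward |
| Complication | suspension or exit | not addressed | same |
| Poor compliance, prohibited drug | suspension or exit | not addressed | same |

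From this text a site cannot tell whether the week 12 and week 24 measurements are still taken.

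**Sample size, as context (section 2.4).** Pooled variance = (0.71² + 0.85²)/2 = 0.6133, so SD = 0.783 L. Difference = 3.81 − 3.07 = 0.74 L. With 90% power and two-sided 0.05, n = (1.960 + 1.282)² × 2 × 0.6133/0.74² = 23.5 per arm, against the stated 23. The one-sided 0.05 written there gives 19.2, which is a separate matter. Drop-out: 23/0.90 = 25.6, so 26 as stated; 30 are recruited. Thus 30 − 23 = 7 exits per arm (23%) still leave 23.

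Power among patients still observed is Φ(0.74/(0.783 × √(2/n)) − 1.96):

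| Exits (assumed) | Left per arm | Two-sided power |
|---|---|---|
| 10% | 27 | 93% |
| 20% | 24 | 91% |
| 30% | 21 | 86% |
| 40% | 18 | 81% |

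Loss of power is therefore not the main issue. Selective loss is.

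**FVC (all inputs assumed).** If an arm of 30 has e exits and each exiting patient then loses L litres that are never recorded, the arm's mean decline is understated by e × L/30. With L = 0.5 L:
- 3 exits in control: 3 × 0.5/30 = 0.050 L
- 1 exit on MMD: 1 × 0.5/30 = 0.017 L
- shift in the difference: 0.033 L, against MMD

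Reversing the split gives 0.033 L in favour of MMD, and equal exits with equal losses give none. Each additional exit in one arm adds 0.5/30 = 0.017 L. Relative to the planned difference, 0.033/0.74 = 4.5%; the share is larger if the true effect is smaller.

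**Exacerbation count (assumed, limiting case).** Suppose every exacerbation ended observation. Counts would be capped at one, with mean 1 − exp(−λ) for a Poisson mean λ per 24 weeks. Assume a true rate ratio of 0.5:

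| Control λ | True difference | Capped difference | Capped ratio | Expected exits of 30, control / MMD |
|---|---|---|---|---|
| 0.1 | 0.05 | 0.046 | 0.51 | 2.9 / 1.5 |
| 0.3 | 0.15 | 0.120 | 0.54 | 7.8 / 4.2 |
| 0.5 | 0.25 | 0.172 | 0.56 | 11.8 / 6.6 |
| 1.0 | 0.50 | 0.239 | 0.62 | 19.0 / 11.8 |

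The distortion is small at low rates and material at high ones. Only exacerbations judged to meet the exit criteria would act this way, so the table bounds the effect of capping alone.

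**The case against.** The strongest reply is that this is loose drafting in a condensed article. Sections 2.8 and 3.5 can be read together: a serious event leads to suspension of the intervention after evaluation, and exit is the other option on the list. Counting exacerbations at three visits suggests that patients are meant to stay after a first event. Section 3.3 runs safety tests to the end of the study. Visit procedures after discontinuation are often left to the full protocol.

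Much of this is fair. The joint reading is possible, and the absence of visit detail alone would be no finding. What remains is that section 2.8 itself names exit from the study, attaches it to no particular item, and describes only conventional treatment afterwards. Section 3.3 does not settle the matter, because it ties adverse event recording to the treatment period.

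Three stronger readings are tempting, and the documents do not support them:
- *That an exacerbation necessarily removes the patient.* No section classes it as a serious adverse event or a complication. The Introduction's examples of complications do not include it, although that list is not exhaustive. Some exacerbations could meet the trigger; the text does not say that all do.
- *That intention to treat becomes impossible.* All 60 patients can formally be analysed as allocated with carried-forward values. Exit creates missing data; it does not exclude anyone from the analysis.
- *That a few exits exhaust the drop-out allowance.* With 30 recruited against 23 needed, they do not.

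**Conclusion.** The point holds in a limited form. The exit criteria do not distinguish stopping treatment from leaving the study, and they do not sit clearly with sections 3.5 and 3.6. Followed as written, they may end observation of both primary outcomes for reasons related to prognosis and treatment. That undermines an intention-to-treat analysis based on observed outcomes, but does not prevent one in form.

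The size is unknown, because the documents give no exit rate, exacerbation rate or FVC loss after an event. The 0.033 L shift and the capped counts rest wholly on assumptions and show scale only. The direction is not fixed either. For FVC, the arm that loses more declining patients looks better than it is. For exacerbations, ending observation at the event shrinks a true difference, while more exits for other reasons in one arm lower that arm's count. The loss of FVC power is modest at plausible exit rates, so the case rests on bias.

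**What to change.** Reconcile sections 2.8, 3.5 and 3.6, and add three statements:

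1. Stopping study treatment and leaving the study are separate. Each item in section 2.8 should say which of the two it leads to.
2. Patients who stop study treatment for any reason other than withdrawn consent to follow-up still have the scheduled week 4, 12 and 24 FVC, exacerbation and adverse event assessments, and are analysed as randomised with those data.
3. An acute exacerbation is an outcome event and does not by itself end data collection.

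The clinical rules for stopping treatment are for the sponsor, and nothing is proposed on them here.

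The cost is amendment wording and keeping visits that are already scheduled for the patients who stop early; section 3.4 already makes examinations and transport free to participants. The carried-forward rule would then apply to fewer values.

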### Chinese herbal medicine

2.9

The prescription in experiment group is MMD, while MMD mimetic agent will be placebo in control group. All the Chinese medicine will be produced by the Sichuan Green Pharmaceutical Technology Development Co, Ltd (Sichuan, China). Chinese herbs of MMD are Radix Ophiopogonis japonici (Maimendong) 10 g, Pinellia ternate (Banxia) 15 g, Radix Ginseng (Renshen) 5 g, Polygonum cuspidatum (Huzhang) 10 g, Ligusticum (Chuanxiong) 10 g, Salviae Miltiorrhizae Radix Et Rhizoma (Danshen) 15 g and licorice (Gancao) 5 g. The herbs in the formula are manufactured to granules by the company. All the drugs will be consistent with the national standards of quality. The granules of each formula are divided into 3 parts equally, and then packaged into 3 small sachets. Placebos will be made of non-active ingredients. The placebo will be identical with the MMD granules in characteristics such as weight, appearance, smell and taste.

## Intervention

3

### Treatment plan

3.1

The subjects in both groups will be treated with routine western medicine, and the treatment plan will be based on the consensus of Chinese experts in the diagnosis and treatment of IPF^[7]^: Pirfenidone capsule (trade name: Esri specification: 100 mg ∗ 54 manufacturer: Beijing Contini Pharmaceutical Co., Ltd.). In the first week, 200 mg each time will be taken 3 times a day for a week. In the second week, 400 mg each time will be taken 3 times a day for 4 weeks. In the sixth week, 600 mg each time will be taken 3 times a day for long-term maintenance.

Experiment group: subjects in the experimental group will receive MMD granules with a small sachet 3 daily for 24 weeks, after breakfast, lunch and dinner respectively. The granules of each sachet will be dissolving in 100 ml boiled water.

Control group: patients in the control group will be given placebo granules with a small sachet 3 daily for 24 weeks. The proceeding will be similar with the experiment group.

### Outcomes measure

3.2

The following outcomes for the subjects will be assessed by independent researchers who do not know the allocation.

Primary outcomes: The primary outcomes are the change from the baseline in FVC at week 4, 12, 24 and times of acute exacerbations at week 4, 12, 24.

Secondary outcomes:

1.The change from baseline in the St. George's respiratory questionnaire total score at week 4, 12, and 24.2.The change from baseline in forced expiratory volume in 1 second percentage/FVC at week 4, 12, and 24.3.The change from baseline in diffusing capacity of Carbon monoxide at week 4, 12, and 24.4.The change from baseline in brain natriuretic peptide at week 4, 12, and 24.5.The change from baseline in curative effect of TCM syndrome at week 4, 12, and 24.

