### Sample size calculation

2.4

Calculation of the sample size was based on the primary outcome variable, forced vital capacity (FVC). According to previous study,^[20]^ the mean of FVC in control group was 3.07 L and the standard deviation was 0.71 L after taking Pifenidone. With oral MMD plus Pifenidone, the mean in experiment group was 3.81 L, and the standard deviation was 0.85 L. We employed following formula to calculate the sample size in each group: n *= (μ*_*α*_* + μ*_*β*_*)*^*2*^ *×* *(1+1/k)* *×* *σ*^*2*^*/ (μ*_*2*_*-μ*_*1*_*)*^*2*^, where *σ*^2^ is overall variance, which was estimated as sample variance *s*^2^ just like the formula *s*^*2*^*= (s*_*1*_^*2*^* + ks*_*2*_^*2*^*) / (1 + k)*. The proportion of subjects between the experiment and control groups was set to 1:1 (k = 1). The study was designed to have a power of approximately 90% and 1-side level of significance of 0.05 (a = 0.05, β = 0.1). *μ*_2_, *μ*_1_, *s*_1_, and *s*_2_ are mean and standard deviations in the control and experiment groups respectively. Twenty-three patients are needed in each group based on the formula mentioned above. Considering a 10% of drop-out rate, approximately 26 patients should initially be recruited in each group. In the study, 30 subjects will be recruited in each group actually, with a total of 60 subjects.

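### Six primary comparisons (FVC change and acute exacerbations, each at weeks 4, 12 and 24) share one two-sided .05 level, and no endpoint or visit is named as decisive

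*Protocol article*

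**What the plan says.** All references are to the protocol article.

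- **Section 3.2 (Outcomes measure)** gives the primary outcomes as "the change from the baseline in FVC at week 4, 12, 24 and times of acute exacerbations at week 4, 12, 24". The abstract's Methods paragraph lists the same two outcomes at the same three visits. Neither place puts one outcome or visit ahead of the others.
- **Section 3.6 (Statistical analysis)** states that all P-values "will be for 2-sided distributions, with a significant level of .05 for α". It names simple two-group tests: t-tests or non-parametric tests for measurements, while "the count data will be tested using a Chi-square test or Fisher exact probability method". Analysis is by intention to treat, with the last recorded value carried forward.
- **Section 2.4 (Sample size calculation)** calls FVC the primary outcome variable, in the singular, and sizes on it alone. No visit is named. The inputs are that "the mean of FVC in control group was 3.07 L and the standard deviation was 0.71 L" and that "the mean in experiment group was 3.81 L, and the standard deviation was 0.85 L", with a "power of approximately 90% and 1-side level of significance of 0.05". The results are 23 per group, 26 after 10% dropout, and 30 per group actually recruited.
- **Section 4 (Discussion)** says what would follow if the results are positive, but does not define a positive result.

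**The concern.** Two outcomes at three visits make six primary comparisons. With one .05 level for each and no order among them, the stated rule does not hold the overall false-positive rate at .05. After the data are in, a report could rest on whichever of the six reached significance, and a reader could not tell from the protocol whether that was the result meant to answer the question.

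The sizing adds to the problem. It supports one FVC comparison, yet exacerbations stand as an equal primary outcome with no power consideration at all. A non-significant exacerbation result would say very little, and a significant one would be hard to interpret.

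**Working it through.** **1. The plan's own sample size.** Inputs from section 2.4: difference 3.81 − 3.07 = 0.74 L; pooled SD √[(0.71² + 0.85²)/2] = 0.783 L; power 90%; ratio 1:1. The formula is n = 2 × [0.783 × (z_α + z_β)/0.74]².
- Two-sided .05: n = 23.54, rounded up to 24.
- One-sided .05, as section 2.4 states: n = 19.18, rounded up to 20.

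The stated 23 fits the two-sided calculation to within rounding. The one-sided label is a separate inconsistency. What matters here is that the figure covers one FVC comparison and nothing else.

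**2. Upper case for the family-wise error.** Six independent tests, each spending the full .05: 1 − 0.95⁶ = 26.5%. The Bonferroni bound is 6 × .05 = 30%. Neither is realistic, because visits within an outcome are correlated and exact tests on few events do not spend their full 5%.

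**3. The three FVC visits alone.** The documents give no between-visit correlation, so a range is assumed. Independent visits give 1 − 0.95³ = 14.3%. Simulated correlated normal test statistics give:

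| Assumed correlation | At least one of three FVC tests significant |
|---|---|
| 0.5 | 12.5% |
| 0.7 | 10.9% |
| 0.9 | 8.4% |

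**4. What the exacerbation tests add.** Assume Fisher's test on patients with at least one event, 30 v 30. Its actual size, computed exactly, is 0.1% per test at a true risk of 5% in both arms, 0.9% at 10% and 2.2% at 20% (assumed risks). Three cumulative exacerbation tests were then simulated with the three FVC tests, FVC correlation 0.5 to 0.9, outcomes independent:

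| Assumed 24-week risk | Any of six significant |
|---|---|
| 5% | about 8–13% |
| 10% | about 9–13% |
| 20% | about 11–15% |

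At risks of 5% to 10% nearly all the error comes from FVC. At 20% the exacerbation tests add two to three percentage points. These rates are two-sided, so false results favouring the decoction make up about half of them.

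**5. Power for exacerbations.** Exact Fisher power at 30 v 30 is 9.6% for 20% v 10% and 1.9% for 10% v 5% (assumed risks).

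**6. Cost of the alternatives for FVC.** With last value carried forward, 30 per arm are analysed. Noncentral-t power for 0.74 L with SD 0.783 L is 94.9% at two-sided .05 and 81.9% at .05/6 = .0083.

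**The case against.** Several points can be made for the plan.

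- **No rule says that any one of six is enough.** This is true. A reader might infer that the trial declares success on any significant result, but the article does not say so. The three visits may be partly an assessment schedule, since every secondary outcome carries the same weeks. What stands is that the article labels all six as primary and states no rule of either kind. The hypothesis in section 4 joins its aims with an and, but it includes quality of life, a secondary outcome, so it is not an all-must-succeed rule.
- **A multiplicity procedure may be in an analysis plan that is not shown.** Its absence is therefore not the finding. The finding is what the article fixes: an unranked list of six and one .05 level for every P-value.
- **Section 2.4 points to FVC as the lead.** It does so in part, but it names no visit and does not demote exacerbations.
- **The error rate is well below 26.5%.** This is correct. A reader might quote that figure as the trial's error rate, but it needs six independent tests that each spend 5%. Sparse exacerbation counts rule that out under Fisher's test.
- **The exacerbation test is not fixed.** Chi-square or Fisher is allowed, and times of exacerbation could mean counts per patient. The figures in steps 4 and 5 are therefore conditional on comparing patients with an event by Fisher's test.
- **Week 4 falls during pirfenidone titration.** A reader might add this as an argument against that visit. Both arms titrate alike, so it has no bearing on this point.

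The Discussion also calls the trial preliminary and concedes that the sample is small. This lowers the stakes but does not tell a reader which result counts.

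**Conclusion.** The concern holds in a limited form. The article names six unranked primary comparisons, tests each at two-sided .05, and sizes for one. The chance of at least one false significant primary result is about 8% to 15% in place of 5%, and the FVC visits account for most of it. That range rests on assumed between-visit correlations of 0.5 to 0.9, assumed 24-week exacerbation risks of 5% to 20%, independence between the two outcomes, and Fisher's test at 30 v 30. The FVC-only range of 8.4% to 12.5% needs only the correlation assumption and is already above .05.

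If exacerbations are compared as patients with an event, power of about 10% or 2% under the assumed risks means they cannot support a primary claim at this size. The FVC power figures take the document's means and SDs at face value. Those describe FVC after treatment, whereas the primary outcome is change from baseline.

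**What to change.** In section 3.2 and the abstract, name one primary comparison: change from baseline in FVC at week 24, tested at two-sided .05. This matches the single-FVC sizing in section 2.4, which should then name the visit. Make FVC change at weeks 4 and 12 secondary. Make acute exacerbations secondary and analyse them once over the 24 weeks, so that overlapping counts are not tested three times.

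The cost is a wording change in the protocol and a registry update, both before unblinding. No patients or visits are added. On the document's own inputs, FVC power stays at about 95% with 30 per arm. Keeping all six with a Bonferroni split would lower it to about 82%. A fixed testing order or one joint test across visits would also control the error, but a single primary is simpler and fits the sizing already done. The downside is that the trial gives up a formal primary claim on exacerbations.

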### Safety assessment

3.3

With recorded in Treatise on Febrile Diseases, 1 of the 4 Classics of TCM, the Maimendong decoction has been used for nearly 2000 years. Chinese herbs dosage of the MMD in this clinical trial will be accordance with the People's Republic of China Pharmacopeia (2015 edition). Moreover, the vital signs and electrocardiogram of subjects will be monitored by doctors, and we will do laboratory tests including blood, urine, stool routine, liver function, renal function to assess the safety of MMD from the enrollment to the end of this study. Adverse events will be recorded at any time they occur during the treatment period.

